## Abstract

**Background:**

Combination of chemotherapies (fluoropirimidines, oxaliplatin and irinotecan) with biologic drugs (bevacizumab, panitumumab, cetuximab) have improved clinical responses and survival of metastatic colorectal cancer (mCRC). However, patients’ selection thorough the identification of predictive factors still represent a challange. Cetuximab (Erbitux®), a chimeric monoclonal antibody binding to the Epidermal Growth Factor Receptor (EGFR), belongs to the Immunoglobulins (Ig) grade 1 subclass able to elicite both in vitro and in vivo the Antibody-Dependent Cell-mediated Cytotoxicity (ADCC). ADCC is the cytotoxic killing of antibody-coated target cells by immunologic effectors. The effector cells express a receptor for the Fc portion of these antibodies (FcγR); genetic polymorphisms of FcγR modify the binding affinity with the Fc of IgG1. Interestingly, the high-affinity FcγRIIIa V/V is associated with increased ADCC in vitro and in vivo*.* Thus, ADCC could partially account for cetuximab activity.

**Methods/design:**

CIFRA is a single arm, open-label, phase II study assessing the activity of cetuximab in combination with irinotecan and fluorouracile in FcγRIIIa V/V patients with KRAS, NRAS, BRAF wild type mCRC. The study is designed with a two-stage Simon model based on a hypothetical higher response rate (+ 10%) of FcγRIIIa V/V patients as compared to previous trials (about 60%) assuming ADCC as one of the possible mechanisms of cetuximab action. The test power is 95%, the alpha value of the I-type error is 5%. With these assumptions the sample for passing the first stage is 14 patients with > 6 responses and the final sample is 34 patients with > 18 responses to draw positive conclusions. Secondary objectives include toxicity, responses’ duration, progression-free and overall survival. Furthermore, an associated translational study will assess the patients’ cetuximab-mediated ADCC and characterize the tumor microenvironment.

**Discussion:**

The CIFRA study will determine whether ADCC contributes to cetuximab activity in mCRC patients selected on an innovative immunological screening. Data from the translational study will support results’ interpretation as well as provide new insights in host-tumor interactions and cetuximab activity.

**Trial registration:**

The CIFRA trial (version 0.0, June 21, 2018) has been registered into the NIH-US National Library of Medicine, ClinicalTrials.gov database with the identifier number (NCT03874062).

## Background

Colorectal carcinoma is a highly incident neoplasm in Western countries with more than 200,000 new cases diagnosed each year in Europe. About 30 % of patients presents with a metastatic disease [1, 2]. In the last 10 years, significant progress has been made in the treatment of metastatic colorectal cancer (mCRC) due to the the introduction of chemotherapy (CT) containing oxaliplatin and irinotecan. The addition of each of the two chemotherapeutics to fluoropyrimidines has increased the objective response rates and improved the overall survival. In addition, the combination of polyCT and new biological drugs (bevacizumab, cetuximab and panitumumab), has doubled the median survival of mCRC patients [3].

Cetuximab (Erbitux®) is a chimeric monoclonal antibody belonging to the Immunoglobulins (Ig) grade 1 subclass [4]. It blocks the binding of the endogenous ligands of EGFR (Epidermal Growth Factor Receptor), thus inhibiting receptor function. EGFR-dependent signal transduction pathways are involved in the control of proliferation, cell survival, angiogenesis and cell migration [5]. Cetuximab binds to EGFR with an affinity that is 5 to 10 times higher than that of endogenous ligands. The drug is indicated for the treatment of patients with mCRC with non-mutated (wild-type) RAS (RAt Sarcoma) oncogene both in combination with CT and monotherapy in patients who have failed oxaliplatin and irinotecan. The mutation of the RAS gene makes it constitutively activated and therefore not susceptible to EGFR inhibition. In mCRC, the incidence of mutations in the RAS gene is between 30 and 50% [6]. Recent evidence shows that patients with non-mutated RAS mCRC have a significantly greater chance of responding to cetuximab or a combination of cetuximab and CT [7].

### Rationale for evaluating FcγR polymorphisms in mCRC

One of the mechanisms of action of cetuximab is the stimulation of ADCC (Antibody-Dependent Cell-mediated Cytotoxicity). ADCC is mediated by immunoglobulins that bind to cellular targets and makes them sensitive to recognition and destruction by immunologic effectors (Natural Killer, macrophages, myeloid-derived cells, etc.) [8]. The effector cells, particularly the Natural Killers (NK), express receptors for the Fc portion of these antibodies (FcγR). The binding affinity between FcγR and Fc portion of the immunoglobulins is critical for the target cell recognition and the extent of the immunologic response [9, 10]. In the general population, genetic polymorphisms of FcγR have been described to modify the binding affinity of the IgG1 Fc fragment [10]. The polymorphisms identified for FcγRIIa (or CD32, predominantly expressed on macrophages) and FcγRIIIa (or CD16, expressed on NK cells and macrophages) are histidine (H)/arginine (R) at position 131 and valine (V)/phenylalanine (F) at position 158, respectively. In recent years, in vitro [11, 12] and in vivo studies [13] have demonstrated that cetuximab induces an NK cells-mediated ADCC against colon cancer cells independently of KRAS (Kirsten RAt Sarcoma) status. Conversely, clinical studies have shown that FcγRIIa-131H/H and FcγRIIIa-158 V/V genotypes (simplified here as FcγRIIa H/H and FcγRIIIa V/V) are associated with improved response and efficacy in follicular lymphomas and metastatic breast carcinomas treated with rituximab and trastuzumab [14–16], respectively. Contrasting results have been reported in mCRC treated with cetuximab [17, 18]. The variability of these results may depend on methodological issues such as the absence of NRAS (Neuroblastoma-Rat Sarcoma) and BRAF (B- Rapidly Accelerated Fibrosarcoma) oncogene mutations’ assessment, populations’ heterogeneity or the lack of characterization of the tumor microenvironment (TM) with particular emphasis to a subset of CD163+ macrophages (M2 macrophages) producing an array of anti-ADCC molecules (e.g. pro-angiogenic and immunosuppressive factors) [19]. We previously showed that the FcγRIIIa V/V genotype (high affinity Fcγ receptor) correlates with better clinical response and improved PFS (Progression Free Survival) in patients with mCRC treated with cetuximab [20, 21], as described by Bibeau et al. [18].

### Previous results of folfiri plus cetuximab in first-line treatment of mCRC

Cetuximab is active and well tolerated in the first-line treatment of mCRC in association with fluoropyrimidine and irinotecan as demonstrated in the randomized, phase III, EMR 62202013 trial [22] in which the combination of cetuximab and irinotecan plus 5-fluorouracile infusion/folinic acid (FU/AF) was compared to CT only. The proportion of non-mutated KRAS patients was 64%. The response rate (RR: complete plus partial responses/number of evaluable patients) was 46.9% (CI: 42.9–51.0) in the CT/cetuximab arm, significantly higher (*p* = 0.0038) than that of the CT arm (38.7%; IC: 34.8–42.8). Odds ratios of subgroup analyses showed that, in the KRAS wt population, the RR of the cetuximab arm was significantly higher (59.3% vs 43.2%, odds ratio 1.91, 95% CI: 1.24–2.93). Furthermore, the association was able to improve PFS with a HR of 0.85 (IC: 0.726–0.998, *p* = 0.0479). The most common grade 3–4 toxicities in the combination arm were diarrhea (15.7% CT plus cetuximab vs 10.5% CT, *p* = 0.008) and those related to cetuximab infusion (2.5% CT plus cetuximab vs. 0% CT, *p* < 0.001). In the phase III, FIRE-3 study, mCRC patients carrying KRAS wt were randomized to folfiri plus cetuximab or folfiri plus bevacizumab first-line treatment [23]. The RR in the cetuximab group was 62.0% (95% CI: 56.2–67.5) and the median PFS was 10.0 months (95% CI, 8.8–10.8). Safety profile was not different from that previously described, with the most common grade 3–4 toxicities being haematologic (25%), skin reactions (26%), and diarrhoea (11%). The proportion of patients achieving an objective response did not significantly differ between the two groups.

### The current therapeutic context of mCRC and CIFRA hypothesis

Recent meta-analyses [24, 25] have evidenced the role of colon tumor side (rigt vs left) as a predictive factor for response to therapy [26]. Accordingly, the RAS wt tumors deriving from the left colon would be more responder to CT in association with anti-EGFR drugs as compared to the right-sided neoplasms. However, the treatment of the RAS wild-type mCRC is currently based on the use of CT doublets (fluoropyrimidine and oxaliplatin or irinotecan) and biological drugs (bevacizumab, panitumumab, cetuximab). This concept is well expressed in the ESMO (European School of Medical Oncology) guidelines [27] in relation to the diversity of the initial treatment intent, suggesting the use of CT doublets and anti-EGFR (panitumumab or cetuximab) when the main objective is a rapid tumor shrinkage. The NCCN guidelines (National Comprehensive Cancer Network v3.2018) contemplate the use of CT and anti-EGFR, panitumumab or cetuximab, in first or second line therapies in mCRC patients whose primary tumor is localized to the left colon. At present, however, due to a lack of sequence studies with high cross-over rates between biologic drugs, it is not possible to state the best biological drug to be used in first-line.

Here we propose the administration of folfiri (fluorouracile and irinotecan) plus cetuximab in patients selected on the FcγRIIIa V/V genotype. In summary, the CIFRA study is set on a hypothetical higher response rate of FcγRIIIa V/V patients than those reported in previous trials (about 60%) and assumes that ADCC is one of the possible mechanisms of cetuximab action. Furthermore, in this immunologically selected cohort, the different responses associated to tumor side (right vs left) could be non existent or attenuated. CIFRA study results could contribute to ameliorate patients’ selection and definitively address the ADCC and FcγR polymorphisms role in cetuximab activity.

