## Methods and design

CIFRA is a single arm, single center, open-label, phase II study, assessing the activity of cetuximab in combination with folfiri in FcγRIIIa V/V patients with KRAS, NRAS, BRAF wild type mCRC. It will be conducted at the academic hospital Istituto Nazionale Tumori di Napoli, IRCCS “G. Pascale” in Naples (Italy). The study includes also biomarkers’ analysis (cetuximab-mediated ADCC, TM characterization).

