### Objectives

The primary objective is to evaluate the role of the molecular and immunologic selection of patients on response to folfiri and cetuximab in patients with mCRC. The response will be evaluated according to Response Evaluation Criteria In Solid Tumors (RECIST) criteria, version 1.1 [28].

Secondary objectives are the safety, the responses’ duration, the progression-free (PFS) and overall survival (OS). Toxicity will be graded according to the Common Terminology Criteria for Adverse Events (CTCAE) of the National Cancer Institute, version 4.0, June 14, 2010. Response duration will be measured from the time of documented objective response (CR or PR) until documented tumor progression (see also “Response and toxicity assessment” section). PFS will be determined from the data of treatment start untill progression (defined according to RECIST), OS untill death from any cause. Tertiary and correlative objectives consist in exploratory studies of biological markers as predictors of outcome (see the “Tranlsational research” section).

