### Study design and statistical analyses

Sample size is based on a two-stage study design by Simon [29] with activity as primary end-point.

The null hypothesis of a not relevant response rate (40%) will be tested against an alternative response rate hypothesis of 70% with a one-tailed test. The test power is 95%, the alpha value of the I-type error is 5%. With these assumptions the sample for passing the first stage is 14 patients with > 6 objective responses. The final sample is 34 patients with > 18 objective responses to draw positive conclusions.

The populations considered for the analysis are described as follows. Safety Population (SP) is defined as all patients receiving at least one dose of treatment. Incorrect treatment or anticipation of the end of treatment are not reasons for exclusion from the SP. Efficacy Evaluable (EE) population is represented by patients who will receive at least one post-baseline assessment of the primary endpoint [28].

All patients who will receive at least one dose of treatment will be included in the descriptive statistics. The basic characteristics of the recruited patients will be reported for the categorical variables as total number and percentage and for the continuous variables as mean and standard deviation or median and interquartile range. Descriptive statistics of patients excluded from the SP and EE will also be carried out. Summary statistics on treatment will be compiled including information on dose changes, interruptions, non-compliance, reasons for protocol deviation, and treatment duration. The analysis on safety will be carried out on the SP. All the information necessary to identify the occurrence of adverse events will be used in the analysis and summarized through descriptive statistics. The confidence intervals will be calculated at 95%. Time-to-outcome will be described by Kaplan-Meier curves.

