### Therapeutic schedule

The therapeutic schedule [22, 23] is represented by cetuximab 400 mg/mq intravenously (iv) with a loading dose of 400 mg/mq at the first cycle followed by 250 mg/mq iv weekly. Cetuximab will be diluted in 500 ml of saline solution and administered by iv infusion in 90 min. The administration of irinotecan will precede that of cetuximab and will consist on a dose of 180 mg/mq diluted in 500 ml of saline solution and administered iv in 60 min. Fluorouracil (5-FU) will be administered at a dose of 400 mg/mq in slow iv bolus at half of lederfolin 200 mg/mq (diluted in 250 ml of saline solution) 2-h infusion. An elastomeric pump with 5-fu 2400 mg/mq in continuous 46 h-infusion will be adminstered after lederfolin. The therapeutic scheme just described is briefly indicated as folfiri/cetuximab. Only at the first administration of CT, irinotecan will not be administered (Fig. 1). This is a peculiar and innovative characteristic of the CIFRA study. ADCC occurs rapidly at the beginning of the therapy because it involves lympocytes subpopulatons (i.e. NK) that do not require immunological priming. Although immunomodulatory effects of irinotecan are not described, it is reasonable and biologically plausible that irinotecan-induced lymphopenia could interfere the ADCC phenomena.

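### The 60% reference rate is KRAS-only and no V/F or F/F patient is treated, so a higher response rate in CIFRA cannot be attributed to FcγRIIIa V/V

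*Protocol article*

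**What the plan says.** All references are to the protocol article.

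- **Source of the benchmark.** Previous results of folfiri plus cetuximab in first-line treatment of mCRC describes two trials. In the first, "in the KRAS wt population, the RR of the cetuximab arm was significantly higher (59.3% vs 43.2" (percent). The second, FIRE-3, randomised KRAS wild-type patients and had 62.0% (95% CI 56.2–67.5) in its cetuximab group. No NRAS or BRAF restriction is mentioned for either figure. The Abstract and the section on the CIFRA hypothesis round these to about 60%.
- **Population and design.** Methods and design describes a single-arm, single-centre study in "FcγRIIIa V/V patients with KRAS, NRAS, BRAF wild type mCRC". Eligibility criteria repeats both selections.
- **Objective.** "The primary objective is to evaluate the role of the molecular and immunologic selection of patients on response to folfiri and cetuximab".
- **Test.** "The null hypothesis of a not relevant response rate (40%) will be tested against an alternative response rate hypothesis of 70% with a one-tailed test", continuing after more than 6 responses in 14 patients and positive with more than 18 in 34.
- **Claims.** The Discussion speaks of a 70% activity, 10 points above earlier results, in patients selected on the FcγRIIIa polymorphism. The Abstract states: "The CIFRA study will determine whether ADCC contributes to cetuximab activity in mCRC patients". The section on the CIFRA hypothesis says that the results could "definitively address the ADCC and FcγR polymorphisms role in cetuximab activity".
- **A further difference.** Therapeutic schedule states "Only at the first administration of CT, irinotecan will not be administered", and presents this as particular to CIFRA.

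**The concern.** The 10-point gain is credited to genotype, but the historical figure differs from CIFRA in mutation status as well. The protocol accepts that this matters: its rationale section lists missing NRAS and BRAF assessment among the possible reasons why earlier FcγR results in colorectal cancer conflict. CIFRA's own comparison with 60% has the same weakness.

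Normally a contrast within the trial would separate the two selections. Here every treated patient is V/V and every treated patient is triple wild-type, so neither factor varies. If the response rate comes out high, the data cannot show whether it reflects the genotype, the removal of NRAS/BRAF mutants, or patient mix at one centre. What is at stake is the conclusion: a positive trial would be read as evidence for selecting patients on FcγRIIIa, and the Discussion already foresees follow-on studies in V/V patients.

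**Working it through.** **1. Reproduce the plan's design.** Inputs from Study design and statistical analyses: p0 = 40%, p1 = 70%, one-sided alpha 5%, power 95%.

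P(positive | p) = Σ over x = 7..14 of Bin(x; 14, p) × P(Bin(20, p) ≥ 19 − x)

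- p = 0.40: 0.0385, with a 0.69 probability of stopping after stage 1.
- p = 0.70: 0.9507.

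An exhaustive search returns 6/14 then 18/34 as Simon's optimal design. The sample size is correct for its stated hypotheses.

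**2. What a positive result says about 60%.** The same formula at p = 0.60 gives 0.699. A regimen that merely matches the benchmark, with no effect of genotype or of NRAS/BRAF exclusion, is declared positive about 70% of the time. The smallest positive result is 19/34 = 55.9%, below the benchmark. Its exact 95% CI, ignoring the two stages, is 37.9–72.8%. Meeting the target with 24/34 = 70.6% gives 52.5–84.9%, which still includes 60%.

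**3. How far NRAS/BRAF exclusion alone could move the rate.** Let f be the share of benchmark patients with NRAS or BRAF mutations and y their response rate. If V/V has no effect:

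RR(all wild-type) = (0.60 − f·y) / (1 − f)

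The documents give neither f nor y. Assumptions: f = 10–25%, y = 25–45%.

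| f | y | RR, all wild-type | Gain over 60% |
|---|---|---|---|
| 10% | 45% | 61.7% | +1.7 |
| 10% | 25% | 63.9% | +3.9 |
| 20% | 35% | 66.3% | +6.3 |
| 25% | 45% | 65.0% | +5.0 |
| 25% | 25% | 71.7% | +11.7 |

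**4. Partial anchoring in the documents.**

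- The first benchmark trial had 46.9% overall in the cetuximab arm and 59.3% in KRAS wild-type patients, who were 64% of patients. If that share applies to the arm, KRAS-mutated patients responded at (0.469 − 0.64 × 0.593)/0.36 = 24.9%. Take this as a low value for y. Take 43.2%, the chemotherapy-alone rate in KRAS wild-type patients, as a high one.
- The Background puts RAS mutation at 30–50%. With 36% KRAS-mutated, f = (RAS − 0.36)/0.64, before any BRAF exclusion.
- RAS 40%: f = 6.3%, gain +2.3 (y = 24.9%) or +1.1 (y = 43.2%).
- RAS 50%: f = 21.9%, gain +9.8 or +4.7.

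The plausible gain thus runs from about one point to the whole hypothesised difference.

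**5. Identifiability.** The trial yields one response proportion, in a group where V/V = yes and triple wild-type = yes for everyone. The reference is KRAS wild-type and, as described, not selected on FcγRIIIa. One difference between two rates cannot be divided between two factors that change together, whatever the value found in step 3.

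**The case against.** - **The primary objective names molecular and immunological selection together.** This is right. A gain from excluding NRAS/BRAF mutants belongs to what that sentence describes, so it would be wrong to read the objective as V/V alone. But evaluating the role even of joint selection needs something to compare with, and the Abstract, the hypothesis section and the Discussion link the gain to V/V specifically.
- **A single-arm phase II trial is an accepted, openly declared design.** Agreed. The point concerns the conclusion and the reference rate, not the absence of randomisation.
- **The strongest word sits in conditional Background prose.** The sentence containing "definitively address the ADCC and FcγR polymorphisms role in cetuximab activity" says that results could do this. That softens it, and the Discussion frames later trials only as possibilities. The Abstract's "The CIFRA study will determine whether ADCC contributes to cetuximab activity in mCRC patients" is not conditional.
- **The ADCC work supplies a contrast.** Partly. ADCC is measured per patient, and the sponsor's earlier series had a range of 0–76% within V/V. A correlation with response is therefore possible inside the cohort. It is exploratory and bears on ADCC; it says nothing on V/V against other genotypes.
- **The high chance of a positive result is not a false-positive rate.** Correct. Rates of 61.7–71.7% give a positive result with probability 0.76–0.97, but rejecting 40% is then the right decision. The figure mainly reflects the 40% null, since it is already 0.70 at a true 60%.
- **Irinotecan timing and tumour side are secondary.** Fair. The documents give no size for the first and no direction either. Reporting by side may be in documents not shown. The point does not rest on them.

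**Conclusion.** The concern holds as a limit on attribution. Against a KRAS-only historical rate, with no V/F or F/F patients treated, CIFRA can estimate the response rate of this regimen in triple wild-type V/V patients. It cannot show that FcγRIIIa V/V produced any excess over 60%. This follows from the design and does not depend on the assumed inputs.

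A reader might infer that NRAS/BRAF exclusion would deliver most of the 10 points. The documents do not support that. The figure is about +2 to +12 points under the stated assumptions, and only about +1 to +2, before BRAF, at 40% RAS mutation.

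Nor should the 70% probability of success at a true 60% be read as an error in the sample size, which reproduces exactly. It shows that meeting the rule is no evidence of superiority over the benchmark. The matter should be corrected because it changes what a positive trial may claim.

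**What to change.** 1. Restate the primary objective as estimating the objective response rate of this regimen in V/V, KRAS/NRAS/BRAF wild-type patients. Replace the Abstract's promise to determine the contribution of ADCC, and the claim to address the polymorphisms' role definitively, with hypothesis-generating wording. Keep the ADCC–response correlation within V/V as exploratory.
2. Interpret the observed response rate and its confidence interval against a KRAS/NRAS/BRAF wild-type reference rate, and re-base the 10-point statement on it. The documents contain no such rate, so the sponsor must source and justify one. If none is adequate, the KRAS-only benchmark should be stated as a limitation.

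Neither change adds patients or alters treatment or the two-stage rule. The cost is a weaker claim and probably a less favourable reference figure.

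Optional: all screened patients are genotyped, so best response could be abstracted from charts for V/F and F/F patients given folfiri/cetuximab at the centre. At 28–36% V/V, filling 34 places means genotyping about 94–121 patients (34/0.36 to 34/0.28), so at most 60–87 are non-V/V, and fewer if some are ineligible or treated otherwise. The 95% half-width for 70% vs 60% is 1.96·√(0.7·0.3/34 + 0.6·0.4/n), about 19–20 points for n = 87 to 60. This would be non-randomised and descriptive only, and the fix does not depend on it.
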